0.1. Schema

Advanced Gastric cancer or

postoperative cases suspicious for recurrence

・Suspicious of PM: 1 to 3 of following three clinical criteria

1) Symptoms

Pain, Abdominal distention, Nausea, Tenesmus

2) Tumor marker

Elevation of CEA and/or CA19-9 and/or CA125

3) Images

Ascites, Thickness of intestinal wall and/or intestinal mesentery.

・ECOG performance status : 0/1/2

・ No bowel obstruction

・ Written Informed consent

CT colonography

0.2. Aim

CTC will be performed aiming at improvement of diagnostic performance in patients in whom peritoneal metastasis/recurrence of stomach cancer is suspected based on physical, laboratory test, and imaging findings, but no definite diagnosis can be made. The presence or absence of deformation suggesting peritoneal dissemination in the large intestinal wall will be diagnosed jointly by the physician in charge and radiologist and correlation with the clinical course will be analyzed.

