0.3. Subjects

1. Histologically diagnosed with stomach cancer by endoscopic biopsy or surgical biopsy.
2. Peritoneal metastasis/recurrence of stomach cancer is suspected based on physical, laboratory test, and imaging findings.
3. The ECOG performance status is 0, 1, or 2.
4. Oral ingestion is possible.
5. Written consent is obtained from the patient.

0.4.Target number of enrollment

The diagnostic sensitivity of CTC has been estimated to be 60%, with a threshold value of 50% and an expected value of 75%. Using Simon’s two-stage method with a one-sided alpha value of 0.05 and a beta value of 0.7, we determined that a sample of 18 patients was required for this study.

1.Aim

In this study, we aimed to use CTC for early detection of PM in patients in whom PM was suspected based on clinical symptoms and general CT findings but not yet diagnosed, and to administer anticancer agents in a timely and effective manner.

2.Background and bases of plan

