2.3. Study design

2.3.1. Endpoint

The primary endpoint of this study was the diagnostic sensitivity of CTC for PM. The secondary endpoints included overall survival (OS) and progression-free survival (PFS). The diagnostic sensitivity of CTC has been estimated to be 60%, with a threshold value of 50% and an expected value of 75%. Using Simon’s two-stage method with a one-sided alpha value of 0.05 and a beta value of 0.7, we determined that a sample of 18 patients was required for this study.

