2.3.2. Patient enrollment expectancy

The recurrence rate of post surgical gastric cancer patients is 10-20%. That will calculate approximately 30 patients a year. Among those cases, five to eight will be predicted to show PM.

3. Patient selection

The patients were cases wherein PM/gastric cancer recurrence was suspected based on physical examination, laboratory tests, and imaging findings, but a definite diagnosis could not be established.

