5.2. Interpretation

Radiological interpretations regarding abnormal deformity and/or thickness of the colonic wall were made by the attending surgeons and radiologists.

6. Predicted adverse events

Along with the procedure of CTC, adverse events such as gastrointestinal perforation, gastrointestinal bleeding and bleeding will be dealt appropriately whenever occurred.

7. Ethical matters

All researchers involved in this study act in conformity to the principles of the Helsinki Declaration (http://www.med.or.jp/wma/) and the Japanese Ethical Guidelines for Clinical Studies(http://www.mhlw.go.jp/topics/2003/07/tp0730-2.html).

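### The primary endpoint, sensitivity of CTC for peritoneal metastasis, has no comparator kept apart from the CTC result, so the estimate is at risk of bias, probably upward

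*Protocol*

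**What the plan says.** Section 2.3.1 of the protocol states: "The primary endpoint of this study was the diagnostic sensitivity of CTC for PM". The test compares sensitivity "with a threshold value of 50% and an expected value of 75" percent, in 18 patients, with "a one-sided alpha value of 0.05 and a beta value of 0.7".

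PM status is unknown at entry. Section 3 (Patient selection) describes patients in whom PM or recurrence was suspected "but a definite diagnosis could not be established". It therefore has to be settled after the CTC.

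The only thing the CTC reading is to be set against is named in section 0.2: "correlation with the clinical course will be analyzed". The readable text gives no criteria for counting a patient as having PM, no follow-up window, and no statement that the judgement is made without the CTC.

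Two places say who reads the scan. In section 0.2 the colonic deformation "will be diagnosed jointly by the physician in charge and radiologist"; in section 5.2 the interpretations "were made by the attending surgeons and radiologists". Section 1 (Aim) couples early detection of PM by CTC with the purpose "to administer anticancer agents in a timely and effective manner".

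**The concern.** Sensitivity is the share of patients who truly have PM in whom CTC is positive. It has no meaning until someone decides, independently of CTC, who has PM. Here the clinicians who know the CTC result also direct the clinical course against which CTC is judged. Three things can then go wrong:

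- **Incorporation.** A CTC-positive patient may be labelled as PM partly because of the CTC.
- **Differential verification.** A CTC-negative patient is recognised as PM only if disease declares itself by other means during a follow-up of unstated length. If it does not, a missed case drops out of the denominator. The protocol's background suggests this can happen: section 2.1.1 says PM is hard to identify by imaging, and section 2.2.1 cites a CT sensitivity of 0.33 from a meta-analysis (a randomised study cited there gives 76.5%).
- **Treatment effect.** If CTC-positive patients are treated earlier, the course used to judge them changes.

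The first two push sensitivity up; the third can push it down. At stake is the only primary result: a comparison with 50% at a one-sided 5% level means little if the denominator depends on the test result.

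**Working it through.** **The plan's own figure.** The null is 0.50, the alternative 0.75, one-sided alpha 0.05 (section 2.3.1). Reading the stated beta of 0.7 as power 0.7, an exact search over Simon two-stage designs gives the minimax design: 7 patients, continue if more than 3 are positive, then 18 in total and pass if more than 12 are positive. Its alpha is 0.0464 and its power 0.7056. So 18 reproduces, and this point does not touch the sample-size arithmetic. The single-stage counterpart, at least 13 of 18, has alpha 0.0481 and power 0.7175. It is used below because it is simpler; two-stage results are shown beside it.

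**Model.** Let s be the true sensitivity, a the probability that true PM is recognised when CTC is positive, and b the same probability when CTC is negative.

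Apparent sensitivity = s·a / (s·a + (1 − s)·b)

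The documents give neither a nor b, so the ratios are assumptions. The protocol states no pass rule; 13 of 18 is derived from its design inputs. All 18 are taken to be patients counted as PM.

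**CTC-negative PM recognised less often, true s = 0.50.** With a = 1 and b = 0.9, 0.5 / (0.5 + 0.5 × 0.9) = 0.5 / 0.95 = 0.526. The chance of passing is the binomial probability of at least 13 of 18 at that value.

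| b/a | Apparent sensitivity | Pass, ≥13 of 18 | Pass, two-stage 7/18 |
|---|---|---|---|
| 1.0 | 50.0% | 4.8% | 4.6% |
| 0.9 | 52.6% | 7.5% | 7.2% |
| 0.7 | 58.8% | 18.1% | 17.5% |
| 0.5 | 66.7% | 41.2% | 40.2% |

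**CTC false positives labelled as PM.** The formula above leaves this mechanism out. With assumed PM prevalence 0.5, specificity 0.8, every false positive labelled as PM and b/a = 1, per patient enrolled: true positives 0.5 × 0.5 = 0.25, false positives 0.5 × 0.2 = 0.10, missed PM 0.25. Apparent sensitivity = 0.35 / 0.60 = 58.3% for a true 50%.

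**Opposite direction: treatment delays overt PM in CTC-positive patients.** With a/b = 0.75:

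- True 50%: 0.375 / (0.375 + 0.5) = 42.9%; chance of passing 1.1%.
- True 75%: 0.5625 / (0.5625 + 0.25) = 69.2%; power falls from 72% to 51% (13-of-18 rule).

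**No bias.** With a = b and no false positive labelled as PM, apparent and true sensitivity agree.

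**The case against.** A reader might infer that CTC findings decide who counts as PM, that CTC is the trigger for treatment, and that sensitivity therefore is inflated. The protocol does not support that as fact. It does not say that PM status is taken from the CTC, does not call the clinical course the formal reference standard, and contains no readable rule that starts treatment on a CTC result. Section 1 states a general aim. It is also silent on masking, so lack of masking is inferred from who reads the scans.

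The direction is not certain either, as the last calculation shows. The 41% figure should not be used as a headline, because it rests on an assumed ratio of 0.5. Overall and progression-free survival are secondary endpoints, so some follow-up is implied, and section 2.1.1 gives about nine months' survival for PM even when treated. Missed PM would often surface, which favours ratios nearer 0.9 than 0.5, although no follow-up length is stated.

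Finally, some pages are not available, and the mechanics of adjudication are often left to an analysis plan that is not shown.

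These objections limit how strongly the point can be put. They do not remove it. Section 2.3.1, which defines the endpoint, is readable and supplies no definition of PM independent of CTC; nor does any other readable section. What counts as PM, judged by whom and over what period, belongs to the design of a diagnostic-accuracy study. An analysis plan written later cannot restore equal follow-up or a judgement made without the CTC.

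**Conclusion.** The point holds as a risk of bias in the primary endpoint. The only stated comparator is not separated from the CTC result, so the estimate is open to incorporation and differential-verification bias, probably upward and possibly downward.

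The size cannot be derived from the document. Under the assumed ratios of 0.9 to 0.5, the upward distortion at a true 50% runs from about 3 to 17 percentage points. Under the assumed reverse ratio of 0.75, the downward distortion is about 7 points at a true 50% and 6 points at a true 75%. Even the mild case, 0.9, moves the false-positive rate above the stated 5%. The conclusion needs no particular ratio: while the two recognition probabilities are uncontrolled, the comparison with 50% cannot be interpreted with confidence. It should be corrected before the primary result is relied on.

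**What to change.** In section 2.3.1, add a definition of PM status with these elements:

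1. PM is decided only from evidence other than the study CTC: histology or cytology where obtained in care, or unequivocal PM on later conventional imaging or from clinical events.
2. The same criteria and one fixed follow-up window apply to CTC-positive and CTC-negative patients. The sponsor should justify the window's length against the roughly nine-month survival in section 2.1.1.
3. The CTC reading is recorded and locked before the outcome is known.
4. Starting anticancer treatment does not count as evidence of PM.
5. PM status is judged on records with the CTC result removed, where possible by an existing investigator who did not read that patient's CTC. Because the attending surgeons take part in the readings, review by the same reader would be masked in name only.
6. Patients whose status stays unresolved, including those who die before confirmation, enter a best-case and worst-case calculation of sensitivity.

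The report should acknowledge that any effect of treatment on the course remains a limitation; so does reliance on conventional imaging of limited sensitivity.

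The cost is protocol wording and some chart review by current staff, with no new procedure and no change to patient management. The estimated sensitivity may turn out less favourable.

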0.3. Subjects

1. Histologically diagnosed with stomach cancer by endoscopic biopsy or surgical biopsy.
2. Peritoneal metastasis/recurrence of stomach cancer is suspected based on physical, laboratory test, and imaging findings.
3. The ECOG performance status is 0, 1, or 2.
4. Oral ingestion is possible.
5. Written consent is obtained from the patient.

0.4.Target number of enrollment

The diagnostic sensitivity of CTC has been estimated to be 60%, with a threshold value of 50% and an expected value of 75%. Using Simon’s two-stage method with a one-sided alpha value of 0.05 and a beta value of 0.7, we determined that a sample of 18 patients was required for this study.

1.Aim

In this study, we aimed to use CTC for early detection of PM in patients in whom PM was suspected based on clinical symptoms and general CT findings but not yet diagnosed, and to administer anticancer agents in a timely and effective manner.

2.Background and bases of plan

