2.2.3. Contrast enema

Since intestinal stenosis occurs as peritoneal dissemination advances in many cases, when stenosis is observed in stomach cancer patients on contrast enema, peritoneal dissemination is strongly suspected. However, the diagnostic sensitivity of contrast enema is unclear when it is performed while the absolute amount of disseminated tumor is still small, even though characteristic findings, such as “striped colon 10)” and “fixed transverse parallel folds 11)”, are observed. Miyagawa 12) reported comparisons between contrast enema and CT findings in 60 patients diagnosed with large intestinal metastasis of stomach cancer. The definite diagnosis of metastasis was made by surgery in 28, autopsy in 5, and clinical judgment, such as imaging, in 27. When 5 mm or more wall thickness on CT was set as a diagnostic criterion, the diagnosis could be made in more than 80%, but the diagnostic sensitivity of enema was 98% (59/60), being superior to that (83% (50/60)) of CT. On the other hand, CT was considered advantageous when the purpose was diagnosis of peritoneal dissemination, because intra-abdominal masses were noted in 62% of the patients and ascites was noted in 37%, showing that the lesions are derived from peritoneal dissemination in many patients. One reason for the absence of overlooking on enema is that the difference between normal and metastatic regions is emphasized by dilating the large intestine by injecting air. If CT images are acquired while air is injected into the large intestine, improvement of the sensitivity of CT for peritoneal dissemination can be expected.

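### The primary sensitivity has no named reference standard independent of CTC: the only stated comparator is a clinical course that the CTC result can shape, which leaves it open to incorporation and differential-verification bias

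*Protocol*

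**What the plan says.** Section 2.3.1 states: "The primary endpoint of this study was the diagnostic sensitivity of CTC for PM". The denominator of that quantity is the number of patients who truly have PM. Section 0.2 describes the population as one in which PM is suspected "but no definite diagnosis can be made", so that number is not known when the CTC is read.

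For what happens after the reading, section 0.2 says only that "correlation with the clinical course will be analyzed". The protocol shown states no other comparator for the CTC call. It names no histology, cytology, operative finding, follow-up window or adjudication as the standard for PM in this study.

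On who reads the scan, section 0.2 has it "diagnosed jointly by the physician in charge and radiologist", and section 5.2 says interpretations "were made by the attending surgeons and radiologists". Neither section says that the call is fixed before the patient's later course is known. Section 1 gives the purpose of early detection as "to administer anticancer agents in a timely and effective manner".

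**The concern.** Taken together, these statements let the CTC result shape the evidence against which it is judged. The clinicians who follow and treat the patient know the CTC call because they helped make it, and the study's aim is that detection should lead to treatment. Two upward routes follow.

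- **Incorporation.** A CTC-positive patient managed as having PM may be counted as PM although nothing but the CTC ever showed it. False positives then become true positives.
- **Differential verification.** PM may be sought and confirmed more completely after a positive CTC than after a negative one. Missed cases then drop out of the denominator.

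A downward route is also conceivable: treatment of a true CTC-positive patient could keep PM from showing on other tests.

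Sensitivity is the only primary endpoint and is set against a 50% threshold. If the verification depends on the test, neither a pass nor a fail against 50% can be read at face value.

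**Working it through.** **The plan's own figure.** Inputs from 2.3.1: threshold 0.50, expected value 0.75, one-sided alpha 0.05, and 0.7, read here as power. An exact search over Simon two-stage designs gives a minimax design of n = 18 (7 patients in stage 1, continue with 4 or more positive, succeed with 13 or more of 18), with alpha 0.0464 and power 0.7056. So 18 reproduces. For simplicity, the figures below use the single-stage rule of 13 or more of 18:

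- P(X ≥ 13 | 18, 0.50) = 0.048
- P(X ≥ 13 | 18, 0.75) = 0.717

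**Assumptions not in the documents.** 60% of entrants have PM; true sensitivity is 50%, the protocol's threshold; all 18 counted patients are PM by whatever rule is used; the CTC specificities are as shown.

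**Route 1, incorporation alone.** Apparent sensitivity = (TP + FP)/(TP + FP + FN), with TP = 0.6 × 0.5 = 0.30, FN = 0.30 and FP = 0.4 × (1 − specificity). At specificity 0.90, FP = 0.04 and the result is 0.34/0.64 = 0.531.

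| Specificity | Apparent sensitivity | P(≥ 13 of 18) |
|---|---|---|
| 0.99 | 0.503 | 0.051 |
| 0.96 | 0.513 | 0.060 |
| 0.916 | 0.527 | 0.075 |
| 0.90 | 0.531 | 0.081 |
| 0.80 | 0.559 | 0.122 |
| 0.60 | 0.605 | 0.222 |

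The documents give no specificity for CTC in PM. The nearest values, in 2.2.1, are 0.96-0.99 across conventional methods in the meta-analysis and 91.6% for CT in the Korean study.

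**Route 2, differential verification alone.** No false positives are counted, all CTC-positive PM is confirmed, and a share v of CTC-negative PM is confirmed. Apparent sensitivity = 0.5/(0.5 + 0.5v).

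| v | Apparent sensitivity | P(≥ 13 of 18) |
|---|---|---|
| 1.0 | 0.500 | 0.048 |
| 0.8 | 0.556 | 0.117 |
| 0.6 | 0.625 | 0.277 |
| 0.5 | 0.667 | 0.412 |

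The documents give no value for v. Section 2.2.1 cites CT sensitivity for PM of 0.33 in the meta-analysis and 76.5% in the Korean study, so incomplete confirmation by later conventional CT is plausible.

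**Downward route.** If a quarter of CTC-positive PM patients were never confirmed because they were treated, a true 0.75 would appear as 0.5625/(0.5625 + 0.25) = 0.692, and power would fall from 0.717 to 0.506. The quarter is purely hypothetical.

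**The case against.** The strongest reply is that the plan does not say what the concern needs it to say. Section 0.2 speaks of a correlation and does not make the clinical course the reference standard for the endpoint in 2.3.1. Section 1 is a general aim. Nothing in section 5 says that a positive CTC alone starts treatment, or that treated patients count as PM. A statistical analysis plan could name a standard independent of CTC, which would remove incorporation. All of this is fair, and it limits the point to exposure to bias. It does not remove the point: no independent standard is named, and a later plan cannot supply a CTC call that was not fixed before the follow-up was known.

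Four stronger readings are tempting, and the documents do not support them.

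- **That the result is biased.** The routes can oppose each other and no rate is given, so only openness to bias can be shown.
- **That incorporation alone could produce false success in most trials.** Adding half-confirmation of CTC-negative PM to the specificities of 0.90-0.60 gives 51-73%, but most of that comes from the half-confirmation, which gives 41% on its own. Incorporation alone gives 5-8% at specificity 0.99-0.90.
- **That follow-up length does not matter.** Confirmation of CTC-negative patients depends on it, and any masking by treatment could last only as long as the response. Section 2.1.1 cites survival of only about 9 months in PM even when treated, so lasting masking is speculative.
- **That the enema study in 2.2.3 shows the problem.** It reports that "The definite diagnosis of metastasis was made by surgery in 28, autopsy in 5, and clinical judgment, such as imaging, in 27". It does not say that the enema entered that judgment or that treatment followed from it, so it is no evidence of incorporation.

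**Conclusion.** The point holds in limited form. The primary sensitivity has no named reference standard independent of CTC. The one stated comparator can be influenced by the CTC result, through clinicians who help read the scan and an aim of treating after detection. The resulting bias would be mainly upward, through incorporation and differential verification; its size and net direction cannot be derived from the documents.

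Under the stated assumptions, incorporation is a small effect if CTC specificity is near the values cited for conventional imaging, and a material one if specificity is 0.80 or lower. Unequal confirmation of CTC-negative PM is potentially the larger of the two. This is a cheap improvement that protects the interpretation of the primary endpoint. It does not show that the study's result is wrong.

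**What to change.** Add to sections 0.2 and 2.3.1:

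1. The CTC call is recorded and locked before any follow-up result is known.
2. A patient counts as having PM only on evidence other than the CTC and other than the start of, or response to, treatment. Acceptable evidence is cytology, histology, operative findings or later conventional imaging, all from routine care. The same rule applies to CTC-positive and CTC-negative patients.
3. The number of unverified patients is reported for each CTC group. Sensitivity is given with unverified CTC-positive patients left out and again with them counted as PM. This is a sensitivity analysis and not a double success criterion, because requiring both to pass would cost power.

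The cost is a few sentences and a field on the case report form, with no extra procedure and no change to treatment. The downside is fewer evaluable PM patients and possibly a less favourable sensitivity. Two limits remain. The rule does not recover PM that is never confirmed in CTC-negative patients, which is why their unverified number must be shown. Later conventional CT is also an imperfect standard that shares some signs with CTC.

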2.1. Object

2.1.1. Object disease

The mortality from stomach cancer is the second highest following that from lung cancer in Japan. It is considered that highly advanced/recurrent stomach cancer reduces the overall treatment outcome and MST of the S-1 group in these patients was 13.0 month in the SPIRITS study 1). Peritoneal metastasis/recurrence was the most frequent as well as being the poorest prognostic recurrence pattern accounting for about half of patients with distant metastasis, and even if they can be treated, only about 9-month survival can be expected (JCOG0106). The cause of poor prognosis of peritoneal metastasis includes the following conditions other than malignancy of cells: A sufficient amount of anticancer drugs cannot be administered because intestinal stenosis and hydronephrosis are likely to occur. Identification by imaging is difficult and initiation of treatment is delayed. The disease may spread to every region in the abdominal cavity and it is difficult to get the entire picture. Since evaluation of treatment is difficult, treatment cannot be rapidly switched when the disease is resistant.

